**Figure 1 Fig1:**
[figure not shown]
Study flow diagram outlining the 18 week enrollment.

### Power analysis

For Aim 1, the UPDRS motor score will be the primary outcome. Our power analysis was calculated based on UPDRS motor data from our previous project comparing FE and VE interventions on UPDRS ratings. We observed a mean (95% confidence interval (CI)) reduction of -5.3 (-18.0, 7.4) in the FE group and 0.4 (-15.3, 16.1) in the VE group from baseline to end of treatment (EOT) at 8 weeks. This corresponds to a difference (improvement, reduction) in means (95% CI) of -4.9 (-20.6, 10.8), standard deviation (SD) of difference = 8.0, P = 0.004. Assuming similar variability for the current proposal, with N = 40 subjects per exercise group, we will be able to detect differences of 5.0 or more between groups on UPDRS with 90% power at the 0.05 significance level, adjusting for 3 group comparisons at each of EOT evaluations. No published data exists for outcomes in Aim 2 or 3 with respect to exercise and PD. In general, with 40 subjects per exercise group, power will be 99 percent to detect differences of 1.2 SDs or more between the groups. For Aims 1-2, comparisons at particular time points power is 90% to detect differences of 1.3 SD, applying a Bonferroni correction for analyzing time points (2 post-intervention times) individually. All calculations assume Tukey adjustment for comparing the 3 groups.

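### The pilot figures behind the sample size contradict each other (difference, interval against P value, and planning SD), and the stated 90% power does not follow from the pilot arms

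*Protocol article*

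**What the plan says.** The Power analysis section of the protocol article makes the UPDRS motor score the primary outcome of Aim 1 and bases the calculation on an earlier comparison of forced exercise (FE) and voluntary exercise (VE). For the change from baseline to 8 weeks it reports a "reduction of -5.3 (-18.0, 7.4) in the FE group and 0.4 (-15.3, 16.1) in the VE group". From this it derives a "difference (improvement, reduction) in means (95% CI) of -4.9 (-20.6, 10.8), standard deviation (SD) of difference = 8.0, P = 0.004".

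The planning statement follows directly: "Assuming similar variability for the current proposal, with N = 40 subjects per exercise group", the trial is said to be able to "detect differences of 5.0 or more between groups on UPDRS with 90% power at the 0.05 significance level". The section adds that the calculations use a Tukey adjustment for three groups, and it mentions a Bonferroni correction for two post-intervention times where time points are compared individually. The Randomization section gives 2:2:1 allocation, so 40, 40 and 20 of 100 patients. The article does not state the number of pilot patients or whether the test is one- or two-sided.

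**The concern.** Three things in two adjacent sentences do not fit together.

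- The difference is not the difference of the two arm means.
- An interval called a 95% CI spans zero by a wide margin, yet stands beside a P value of 0.004.
- The SD given for the difference, and the half-width of its interval, are the same as those implied for the VE arm alone.

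The SD is what matters for design, because it is the quantity carried into the new trial. If a reader cannot tell whether 8.0 is a per-patient SD, the SD of a difference or one arm's SD, the 90% power claim for the primary outcome cannot be checked. The readings give materially different answers.

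**Working it through.** **Inputs**, all from the Power analysis section except the 40/40/20 split (Randomization): FE -5.3 (-18.0, 7.4); VE 0.4 (-15.3, 16.1); difference -4.9 (-20.6, 10.8); SD 8.0; P = 0.004; target 5.0; 40 per exercise arm; alpha 0.05. Two-sided testing is assumed.

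**1. Difference of means.**
- FE minus VE = -5.3 - 0.4 = -5.7.
- The printed -4.9 equals -5.3 + 0.4, so it requires a VE change of -0.4.
- The VE interval has midpoint (-15.3 + 16.1)/2 = +0.4, so the positive sign is built into the interval as well.

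**2. Interval against P value.**
- Half-widths: FE (7.4 + 18.0)/2 = 12.7; VE (16.1 + 15.3)/2 = 15.7; difference (10.8 + 20.6)/2 = 15.7.
- Divided by 1.96: 6.48, 8.01 and 8.01.
- Taken as labelled, the difference has SE 8.01, so z = 4.9/8.01 = 0.61 and two-sided P = 0.54.
- P = 0.004 corresponds to z = 2.88, so at -4.9 it needs SE = 4.9/2.88 = 1.70, a 95% CI of about -8.2 to -1.6.
- Because 15.7/1.96 reproduces the printed SD of 8.0, the ranges are most likely mean ± 1.96 SD.

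**3. Which SD is 8.0?** On the mean ± 1.96 SD reading:
- pooled per-arm SD, equal arms assumed: √((6.48² + 8.01²)/2) = 7.29;
- SD of a difference between two independent patients: √(6.48² + 8.01²) = 10.30.

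Neither is 8.0. The value does equal the VE arm's 8.01.

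**4. Power for 5.0 points, 40 per exercise arm.** SE = SD × √(2/40); noncentrality = 5.0/SE; noncentral t with 97 degrees of freedom (100 patients less 3 groups). The Tukey critical value is the studentized-range quantile divided by √2: 3.366/√2 = 2.380 at 0.05, and 3.753/√2 = 2.654 at 0.025 (0.05 split over two times).

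The plan's own 90% comes first. It reproduces when 8.0 is taken literally as the SD of a difference, so that SE = 8.0/√40 = 1.265 (per-arm SD 8.0/√2 = 5.66), with Tukey at 0.025.

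| Per-arm SD | SE | Noncentrality | Power, Tukey 0.05 | Power, Tukey 0.025 |
|---|---|---|---|---|
| 5.66 (8.0 as SD of a difference) | 1.265 | 3.95 | 94% | 90.0% |
| 6.48 (FE arm) | 1.449 | 3.45 | 86% | 79% |
| 7.29 (pooled) | 1.629 | 3.07 | 75% | 66% |
| 8.0 (as per-patient SD) | 1.789 | 2.80 | 66% | 56% |

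With 8.0 as a per-patient SD, power is about 80% even without any multiplicity adjustment, and 90% under Tukey at 0.05 would need about 69 per exercise arm. For 90% at 40 per arm under Tukey at 0.05, the per-arm SD would have to be about 6.1.

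**The case against.** **The difference may be a sign slip.** The sentence uses one word, reduction, for values of opposite sign. If VE fell by 0.4, then -5.3 - (-0.4) = -4.9 exactly. That is a fair explanation, but the VE mean and its interval are then both printed wrongly. If -5.7 is right instead, the printed difference is the conservative one.

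**P = 0.004 may be correct.** A reader might conclude from P = 0.54 that the pilot evidence fails. The document does not support that. The 0.54 holds only if the range really is a confidence interval, and the half-widths point the other way. If the ranges are SD ranges, they say nothing about precision, and without the pilot numbers 0.004 is neither confirmed nor refuted. What stands is that the label and the P value cannot both be right.

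**The origin of 8.0 is inferred.** It is tempting to say that 8.0 is the VE arm's SD. The article calls it the SD of the difference; the match with the VE arm suggests the other origin but does not prove it.

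**The pilot difference need not drive the target.** A reader might infer that 5.0 was taken from -4.9. The text carries forward only the variability and gives 5.0 as a detectable difference, so the choice between -4.9 and -5.7 does not alter the stated power.

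**The 90% can be reproduced.** It can, as shown, but only with a per-arm SD of 5.66, below both arm SDs implied by the printed ranges (6.48 and 8.01). That shows how the figure may have arisen; it does not justify it.

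**The SD of 10.3 should not be read as a per-arm SD.** Doing so gives power near 42% but counts √2 twice. Used as the SD of a difference, SE = 10.30/√40 = 1.629, which is the pooled case again: 75%.

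**Baseline adjustment may help.** The Data analysis section adjusts for baseline, which could bring the residual SD below the SD of change. The article gives no correlation with which to size this and bases its power claim on the pilot variability.

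**Conclusion.** The pilot summary is wrong as written. Either the VE sign, with its interval, or the difference is in error. The interval called a 95% CI is incompatible with P = 0.004 and is most likely mislabelled. The SD of 8.0 does not follow from the two arms.

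The consequence is for the power claim: at 5.0 points with 40 per exercise arm, Tukey-adjusted power at 0.05 is about 66% to 86% over per-arm SDs of 8.0 to 6.5, and about 75% at the pooled value, against the 90% stated.

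These power figures assume two-sided testing, no dropout, the mean ± 1.96 SD reading of the printed ranges and, for the pooled value, equal pilot arms. The mismatch in the difference and the conflict between the labelled CI and the P value need none of these assumptions beyond the usual normal approximation.

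**What to change.** - Recompute the summary from the pilot data. Print the mean change, SD and number of patients for each arm, the correct FE-VE difference, a 95% CI based on its standard error, and the matching P value with the test used.
- If the present ranges are mean ± 1.96 SD, relabel them so.
- State the planning SD explicitly as the pooled within-arm SD of the change.
- Restate the power for 5.0 points at 40 per exercise arm over SDs of 6.5 to 8.0, naming the sidedness and the multiplicity adjustment used.

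The cost is a re-run of the pilot summaries and the power calculation, plus corrected wording. The downside is that the stated power will be less favourable than 90% unless the pilot data show a smaller SD than the printed ranges imply.

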## Methods and design

### Study design

This single center, prospective, rater-blind, three arm clinical trial will investigate the efficacy of a FE paradigm on motor and non-motor symptoms in individuals with PD. A total of 100 individuals with mild to moderate idiopathic PD will be enrolled. CYCLE Trial protocol is approved by the Cleveland Clinic Institutional Review Board and all participants will sign an informed consent prior to beginning the study. Written informed consent was obtained for any photographs that have been taken for publication. A schematic overview of the enrollment, testing, and intervention is shown in Figure 1.

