### Randomization

Participants will be randomized 2:2:1 into FE, VE, or no-exercise control group. The uneven allocation of subjects was selected due to the promising results of the preliminary data by [name], et al. indicating there is a benefit to cardiovascular exercise that would not been seen in a control group [20,21]. Enrollment will total 18 weeks: two weeks allotted for baseline evaluations, 8 weeks of exercise intervention or control period, and 8 weeks for a follow up period in which the participant is instructed to return to their baseline level of physical activity.

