### Data analysis

Participants in all three groups will be compared descriptively on potentially confounding baseline variables (i.e., age, disease severity, and levodopa equivalent daily dose (LEDD)) to assess the extent of any imbalance across groups. Baseline variables in which there appears to be a clinically important baseline difference, or in which the standardized difference (absolute value of difference in means divided by pooled SD) between any 2 groups is greater than 10% will be included as covariates. P-values from these baseline variable comparisons will not be used to determine the need for covariate adjustment, as that criterion can be misleading.

The FE, VE, and the no-exercise control groups will be compared on each outcome of interest (motor, non-motor) using repeated measures analysis of covariance. For motor and non-motor outcomes, groups will be compared on outcomes at the mid-treatment, EOT, EOT + 4 weeks, and EOT + 8 weeks adjusting for the baseline (on and off medication) period as a covariate. The effects of group, time, and the group-by-time interaction will be assessed for each outcome. In the case of a significant interaction, the groups will be compared at each time point. Tukey’s correction for multiple comparisons will be used. Data will be transformed as needed to meet model assumptions. In addition to p-values, the estimated treatment effect and its 95% CI will be of interest as these data will aid in formulating exercise recommendations and potential benefits. For each hypothesis, significance level will be set at 0.05. Each participant’s change in fitness based on change in peak VO_2_ from CPX testing will be used as a covariate. This will remove the effect of possible differences in improvement in fitness level across the groups from confounding the results. Correlation between LEDD and the time spent within target HR zone during training, amount of work performed, and change in primary outcome variables in motor and non-motor outcomes will be assessed. If the LEDD is significantly correlated with these outcomes, it will be included as a covariate in the related analysis.

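### The time-point power figure for Aims 1-2 (90% at 1.3 SD) does not follow from 40/40/20: 90% power is reached at about 0.88 SD between exercise arms and 1.08 SD against control, and the two-time Bonferroni it assumes is absent from the analysis

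*Protocol article*

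**What the plan says.** The Power analysis section makes three sensitivity statements, and closes with "All calculations assume Tukey adjustment for comparing the 3 groups".

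- Aim 1, with 40 patients per exercise group and an SD of 8.0: "we will be able to detect differences of 5.0 or more between groups on UPDRS with 90% power".
- In general, again with 40 per exercise group: "power will be 99 percent to detect differences of 1.2 SDs or more between the groups".
- For Aims 1-2 at individual time points: "power is 90% to detect differences of 1.3 SD, applying a Bonferroni correction for analyzing time points (2 post-intervention times) individually".

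The Data analysis section describes a repeated-measures analysis of covariance in which "groups will be compared on outcomes at the mid-treatment, EOT, EOT + 4 weeks, and EOT + 8 weeks". Visit-by-visit comparisons follow only if the group-by-time interaction is significant. Tukey's method is the only multiplicity correction named. No Bonferroni over visits appears, and no pair of visits is singled out.

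**The concern.** The third statement has a larger detectable difference than the first two, yet no more power. A correction for two time points costs some sensitivity, but it should not double the detectable difference from 0.625 SD to 1.3 SD, nor bring power down from 99% at 1.2 SD to 90% at 1.3 SD.

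The section says there are no published data on exercise in PD for the Aim 2 outcomes, so these sentences are the only guide to what the trial can detect at a given visit for non-motor outcomes. Someone reading a null result would think that only differences of 1.3 SD or more had been well covered. On the UPDRS, 1.3 SD at SD 8.0 is 1.3 × 8.0 = 10.4 points. The multiplicity rule is also stated one way for planning and another way for analysis.

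**Working it through.** **Inputs.**
- Total: "A total of 100 individuals with mild to moderate idiopathic PD will be enrolled" (Study design).
- Allocation: "Participants will be randomized 2:2:1 into FE, VE, or no-exercise control group" (Randomization). Hence 100 × 2/5 = 40 FE, 40 VE and 100 × 1/5 = 20 control.
- Level: "For each hypothesis, significance level will be set at 0.05" (Data analysis). Two-sided pairwise tests are assumed, as is usual with Tukey.
- Also assumed, because the article gives no figures: no dropout, and no precision gained from covariates or repeated measures.

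**Formulas.** The residual degrees of freedom are 100 − 3 = 97. The Tukey critical value is c = q(1 − α; 3, 97)/√2. For a true difference of d SDs, the noncentrality is λ = d·√(n₁n₂/(n₁+n₂)). Power is P(T > c) for a noncentral t with 97 df, which is close to Φ(λ − c).
- Root term, 40 v 40: √(1600/80) = 4.472. Root term, 40 v 20: √(800/60) = 3.651.
- c = 2.380 at α = 0.05; 2.654 at 0.025 (Bonferroni for 2); 2.906 at 0.0125 (Bonferroni for 4).

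**1. The plan's 90% at 1.3 SD, under its own rules (α = 0.025).**
- FE v VE: λ = 1.3 × 4.472 = 5.814, and λ − c = 3.16. Power is 99.9%.
- Exercise v control: λ = 1.3 × 3.651 = 4.746, and λ − c = 2.09. Power is 98.0%.

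The stated 90% is not reproduced for either contrast.

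**2. Difference detectable with 90% power**, approximately (c + 1.282)/root term; the table gives the exact noncentral t values.

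| Correction | FE v VE | Exercise v control |
|---|---|---|
| Tukey only | 0.82 SD | 1.01 SD |
| Tukey + Bonferroni, 2 times | 0.88 SD | 1.08 SD |
| Tukey + Bonferroni, 4 visits | 0.94 SD | 1.15 SD |

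The stated 1.3 SD is 1.3/0.884 = 1.47 times the FE v VE value and 1.3/1.082 = 1.20 times the control value. Correcting for all four visits does not reach it either. With three equal arms, 90% power at 1.3 SD corresponds to about 19 patients per arm.

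**3. Against the Aim 1 statement.**
- 5.0/8.0 = 0.625 SD. Reading 8.0 as the per-person SD fits the paragraph's own interval: half-width (20.6 + 10.8)/2 = 15.7, and 15.7/1.96 = 8.0.
- The two-time Bonferroni multiplies the detectable difference by 0.884/0.822 = 1.075. If 0.625 SD had 90% power with Tukey, the time-point figure would be about 0.625 × 1.075 = 0.67 SD. The stated ratio is 1.3/0.625 = 2.08.
- The Aim 1 figure does not reproduce either: λ = 0.625 × 4.472 = 2.795, λ − 2.380 = 0.415, and power is 66%.

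**4. The 99% at 1.2 SD (Tukey, α = 0.05).**
- FE v VE: λ = 1.2 × 4.472 = 5.367. Power is 99.8%.
- Exercise v control: λ = 1.2 × 3.651 = 4.382. Power is 97.6%.

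The statement holds for the exercise-arm contrast.

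**5. Planning against analysis.** Planning uses Tukey plus Bonferroni over two unnamed times. The analysis has four post-baseline visits, an interaction gate, and Tukey only. Table 1 schedules the UPDRS motor subscale at all four.

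**The case against.** **The error is on the safe side.** This stands. Every contrast has more power at 1.3 SD than stated, and no sample size rests on the figure. A reader might infer that Aim 2 is underpowered because of this sentence; the calculation shows the opposite.

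**The 1.2 SD figure looks equally suspect.** A reader might call it wrong for 40/40/20, or say that the paragraph errs in both directions. The documents do not support that. The sentence is tied to 40 per exercise group, where power is 99.8%, and the control contrast falls short by only 99 − 97.6 = 1.4 points. Nor does it contradict Aim 1: if 0.625 SD had 90% power, 1.2 SD would have more than 99%.

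**Aim 3.** A reader might extend the fault to the imaging aim. The 1.3 SD sentence is limited to Aims 1-2, and the MRI data section plans a paired t-test and correlations rather than a three-group Tukey contrast.

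**Unstated dropout could rescue the figure.** This stands in part. If 30% were lost from each arm, leaving 28/28/14, the control contrast would have λ = 1.3 × √(28 × 14/42) = 3.972 against c = 2.677 on 67 df, and power of 89.8%. No such loss is stated, the calculation is described at 40 per exercise group, and FE v VE would still have 98.4%. For FE v VE to fall to 90%, about half of each exercise arm would have to be lost.

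**The Bonferroni mismatch may be harmless.** This stands largely. Planning with a stricter correction than the analysis uses is conservative for power, and the interaction gate gives some protection across visits. The two times could also be the visits 4 and 8 weeks after treatment. But the article states both rules, they differ, and the pair is not named. The gate can only lower the overall chance of declaring a visit-level difference. By how much cannot be computed, because no between-visit correlation is given.

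**Conclusion.** The point holds for the 1.3 SD sentence. Under the correction it names, and with 40/40/20, 90% power is reached at 0.88 SD (FE v VE) and 1.08 SD (v control). The stated figure is 47% and 20% too large respectively, and it cannot sit beside the Aim 1 statement in the same paragraph. The missing two-time Bonferroni is a real but secondary inconsistency.

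These values assume two-sided tests, full retention and no precision gain. A gain in precision would lower the detectable differences and widen the gap; dropout would narrow it. The result in SD units does not depend on the UPDRS SD of 8.0. Only the comparison with Aim 1 does.

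This is a correction worth making, with no effect on sample size. The power shortfall in the paragraph lies in the Aim 1 figure (about 66% rather than 90%), not here.

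**What to change.** Choose one multiplicity rule for time-point comparisons and use it in both sections.

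- **If the two-time Bonferroni is kept:** name the two visits, write the correction into the Data analysis section, and replace the 1.3 SD sentence with 90% power at 0.88 SD (FE v VE) and 1.08 SD (v control).
- **If it is not kept:** delete it from the Power analysis section and state 0.82 SD and 1.01 SD, with Tukey only.

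Either way, state the assumptions: 40/40/20 analysed, two-sided, no covariate gain. If losses are expected, recompute at the expected number of completers. Leave the 1.2 SD sentence in place, adding only that power against control is about 97.6%. Do not carry the new figures over to Aim 3. The Aim 1 statement needs its own correction so that the paragraph is coherent.

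The cost is wording only, but the choice of rule should be fixed before outcome data are analysed.

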### Subject enrollment

Participants will be recruited via patient education groups, study literature placement in exam rooms, patient chart reviews by research personnel, and in-service lectures at Cleveland Clinic affiliate and non-affiliate hospitals in the Cleveland-metro area.

Primary inclusion criteria for CYCLE Trial include: clinical diagnosis of idiopathic PD, between 30 and 75 years of age, not currently engaged in physical therapy for their PD or another interventional clinical study, Hoehn and Yahr stage II-III while on antiparkinsonian medication. Primary exclusion criteria include: presence of dementia, previous stroke, any medical or musculoskeletal contraindications to exercise, and existing cardiorespiratory disease as determined by American Heart Association/American College of Sports Medicine exercise pre-participation questionnaire [26,27].

### Cardiopulmonary exercise testing

Following completion of initial screening, participants will undergo cardiopulmonary exercise testing (CPX). CPX protocol is administered by an exercise physiologist from the preventative cardiology department of the Cleveland Clinic. Testing will be completed on a Lode cycle ergometer using MedGraphics CardiO_2_/CP system with Breeze software. The participant will be instructed to take his/her PD medication as prescribed on the day of testing. A 12-lead electrocardiogram will be assessed prior to exercise, continuously during exercise, and during exercise recovery. Participants will exercise at an initial load of 25 Watts, increasing by 25 Watts every two minutes until 100 Watts, and then increasing by 50 Watts every two minutes until the American College of Sports Medicine’s Guidelines for Exercise Testing criteria for test termination are reached [28]. The participant’s peak volume of oxygen uptake (VO_2_) will be calculated as the highest 30 second average of VO_2_ during the CPX test. A Cleveland Clinic cardiologist will interpret the results of the test, and those with normal responses to exercise will be randomized while those with abnormal responses will be advised for further medical work up.

### Randomization

Participants will be randomized 2:2:1 into FE, VE, or no-exercise control group. The uneven allocation of subjects was selected due to the promising results of the preliminary data by [name], et al. indicating there is a benefit to cardiovascular exercise that would not been seen in a control group [20,21]. Enrollment will total 18 weeks: two weeks allotted for baseline evaluations, 8 weeks of exercise intervention or control period, and 8 weeks for a follow up period in which the participant is instructed to return to their baseline level of physical activity.

